# VITamin D supplementation in renAL transplant recipients (VITALE): a prospective, multicentre, double-blind, randomized trial of vitamin D estimating the benefit and safety of vitamin D_3_ treatment at a dose of 100,000 UI compared with a dose of 12,000 UI in renal transplant recipients: study protocol for a double-blind, randomized, controlled trial

**DOI:** 10.1186/1745-6215-15-430

**Published:** 2014-11-06

**Keywords:** Interventional trial, Vitamin D, Renal transplantation, Cancer, Cardiovascular events, Diabetes mellitus

## Abstract

**Background:**

In addition to their effects on bone health, high doses of cholecalciferol may have beneficial non-classic effects including the reduction of incidence of type 2 diabetes mellitus, cardiovascular disease, and cancer. These pleiotropic effects have been documented in observational and experimental studies or in small intervention trials. Vitamin D insufficiency is a frequent finding in renal transplant recipients (RTRs), and this population is at risk of the previously cited complications.

**Methods/design:**

The VITALE study is a prospective, multicentre, double-blind, randomized, controlled trial with two parallel groups that will include a total of 640 RTRs. RTRs with vitamin D insufficiency, defined as circulating 25-hydroxyvitamin D levels of less than 30 ng/ml (or 75 nmol/l), will be randomized between 12 and 48 months after transplantation to blinded groups to receive vitamin D_3_ (cholecalciferol) either at high or low dose (respectively, 100,000 UI or 12,000 UI every 2 weeks for 2 months then monthly for 22 months) with a follow-up of 2 years. The primary objective of the study is to evaluate the benefit/risk ratio of high-dose versus low-dose cholecalciferol on a composite endpoint consisting of *de novo* diabetes mellitus; major cardiovascular events; *de novo* cancer; and patient death. Secondary endpoints will include blood pressure (BP) control; echocardiography findings; the incidences of infection and acute rejection episodes; renal allograft function using estimated glomerular filtration rate; proteinuria; graft survival; bone mineral density; the incidence of fractures; and biological relevant parameters of mineral metabolism.

**Discussion:**

We previously reported that the intensive cholecalciferol treatment (100 000 IU every 2 weeks for 2 months) was safe in RTR. Using a pharmacokinetic approach, we showed that cholecalciferol 100,000 IU monthly should maintain serum 25-hydroxyvitamin D at above 30 ng/ml but below 80 ng/ml after renal transplantation. Taken together, these results are reassuring regarding the safety of the cholecalciferol doses that will be used in the VITALE study. Analysis of data collected during the VITALE study will demonstrate whether high or low-dose cholecalciferol is beneficial in RTRs with vitamin D insufficiency.

**Trial registration:**

ClinicalTrials.gov Identifier: NCT01431430.

**Electronic supplementary material:**

The online version of this article (doi:10.1186/1745-6215-15-430) contains supplementary material, which is available to authorized users.

## Background

### Vitamin D and vitamin D insufficiency in renal transplant recipients

Traditionally, vitamin D has been associated with bone health; its deficiency leads to rickets in children and osteomalacia in adults, and increases the risk of osteoporosis. More recently, vitamin D sufficiency has been associated with a reduced risk of many chronic diseases including type 2 diabetes mellitus (T2DM), cardiovascular diseases, cancers, and infectious diseases. All these diseases are more likely to occur in renal transplant recipients (RTR) than in the general population. Currently, the active form of vitamin D is currently used after kidney transplantation for the prevention of post-transplant bone loss [1] and the treatment of normocalcemic persistent secondary hyperparathyroidism [2–4]. Treatment with active vitamin D or its analogues will not compensate for inadequate 25-hydroxyvitamin D (25OHD), however. 25OHD is a substrate for 1α-hydroxylase (CYP27B1) in the kidney, and also in several extrarenal tissues, and these extrarenal tissues are dependent on adequate levels of 25OHD to ensure adequate local calcitriol production. Although there is no current consensus, vitamin D insufficiency is usually defined as 25OHD levels lower than 30 ng/ml (or 75 nmol/l) [5], because this limit is associated with a decrease in active intestinal calcium absorption [6] and with an increase in secretion of serum parathormone (PTH), which is involved in maintenance of normal serum calcium levels [5]. Furthermore, in interventional studies showing positive effects of vitamin D supplementation, the 25OHD levels reached in the treated groups were generally higher than 30 ng/ml [7].

The vitamin D insufficiency is present in more than 85% of adult RTRs [8]. Causes include: 1) insufficient vitamin D supplementation before and after transplantation; 2) increased 25OHD catabolism induced by immunosuppressive drugs [9] and by post-transplant persistent fibroblast growth factor-23 hypersecretion [10]; and 3) the reduced sun exposure recommended to RTRs to prevent skin cancers [11]. As a result, RTRs are now systematically advised to protect themselves from exposure to solar or artificial ultraviolet (UV) radiation. This represents a serious dilemma, as 80% to 90% of the human body’s requirements for vitamin D result from photosynthesis of the vitamin from 7-dehydrocholesterol in the skin by the action of UVB radiation. Therefore, careful monitoring of vitamin D status and oral supplementation to ensure that vitamin D insufficiency does not occur is of great importance for RTR.

### Supplementation of vitamin D after renal transplantation

Despite the high prevalence of vitamin D insufficiency in RTR, there is no general consensus regarding vitamin D supplementation after transplantation. In one study, [12], it was shown that high doses of vitamin D_3_ (100,000 IU cholecalciferol every other week for 2 months, equivalent to 6,600 IU/day) were able to correct 25OHD insufficiency in RTRs without significant side effects, and this regimen was also associated with a significant decrease in serum PTH concentration. However, this study also indicated that the dose of cholecalciferol used during the maintenance phase (100,000 IU every other month from months 6 to 12 post-transplantation) was insufficient to maintain serum 25OHD concentration above 30 ng/ml in half of patients [12]. Another study showed that 25,000 IU of cholecalciferol once a month failed to correct vitamin D insufficiency in RTRs, suggesting that a higher dose of cholecalciferol is necessary to maintain adequate 25OHD levels after transplantation [13]. The optimal dosage scheme was simulated from the data of a previous study [12] using a population pharmacokinetic approach. In order to maintain 25OHD concentrations between 30 and 80 ng/ml during the first year after renal transplantation, it was estimated that cholecalciferol dosing should be 100,000 IU once a month once correction of vitamin D insufficiency has been achieved [14].

### Anticancer properties of vitamin D

RTRs exhibit an increased incidence of cancers, especially of non-melanoma skin cancers and non-Hodgkin lymphoma. Data from the US Renal Data System indicate that at 3 years after renal transplantation, there is a 7.5% cumulative incidence of non-skin cancers and a 7.4% cumulative incidence of skin cancers in RTRs [15]. The role of vitamin D status in cancer risk has received strong experimental support from the consistent demonstration that activation of the vitamin D receptor (VDR) by locally produced calcitriol induces differentiation [16] and apoptosis [17], and inhibits cell proliferation [18] and angiogenesis [19]. Moreover, vitamin D and its metabolites stimulate mutual adherence of cells and intercellular communication through gap junctions, thereby decreasing metastatic potential and strengthening the inhibition of proliferation that results from tight intercellular physical contacts [20]. Many prospective case–control studies have shown that adults in the highest quantile of 25OHD levels have a decreased risk of colon [21] and breast [22] cancers compared with those in the lowest quantile. Furthermore, the risk of non-Hodgkin lymphoma is reduced by 30% to 40% in adults with high vitamin D intakes [23] or high levels of sun exposure [24]. Finally, retrospective studies suggest an association between low serum 25OHD level and death from cancer [25–27]. It must be mentioned that in a few observational studies a U-shaped (or rather an inverse J-shaped) curve between 25OHD serum levels and the risk of prostate [28], or pancreatic cancer [29] has been found (increased risk for both low and high serum 25OHD levels). However, it is a consensus that causality cannot be established from observational studies, so that randomized controlled trials (RCTs) evaluating the effect of vitamin D supplementation on the risk of cancer (versus placebo) are needed to firmly determine whether low and/or high vitamin D status increases the risk of cancer.

Such interventional studies of vitamin D supplementation in humans have yielded controversial data, however. In the Women’s Health Initiative (WHI) study, 36,282 women were randomized to receive either a placebo or 1000 mg calcium and 400 IU vitamin D_3_ daily. Although a strong negative relationship between baseline 25OHD levels and the incidence of colorectal cancer was found, no reduction in the incidence of cancers was observed in the treated group compared with the placebo group [30]. Of note, adherence to treatment was poor, and cholecalciferol dosage was considered to be too low by many experts in that study. Furthermore, women included in the WHI trial were allowed to continue to take the calcium/vitamin D supplementation that they were taking prior to enrolling in the study, so that some women in the placebo group received more vitamin D during the study than some women included in the calcium + vitamin D group. When the analysis was restricted to those women who were not taking calcium or vitamin D supplementation before the study, a significant reduction in the risk of total and invasive breast cancer, as well as in the risk of total cancer, was found [31]. A 4-year, double-blind, randomized, placebo-controlled trial comprising 1,180 postmenopausal women showed a significant decreased risk of cancers in the group receiving calcium (1,500 mg/day) plus vitamin D_3_ (1,100 IU vitamin D3/day) supplementation [32], whereas another 3-year, double-blind, randomized, placebo-controlled trial comprising 5,292 patients aged over 70 years showed no reduction in cancer incidence with vitamin D_3_ 800 IU per day [33]. To our knowledge, no interventional study has reported that vitamin D supplementation increases the risk of any cancer, although it must be emphasized that the doses used were generally too low and the duration of the studies too short to conclude this definitely.

The potential protective role of vitamin D against cancer risk was also assessed in RTRs [34]. In a cohort of 363 RTRs followed up during 3 to 5 years after transplantation, a higher incidence of post-transplant cancers was observed in patients with pre-transplant 25OHD concentrations less than 10 ng/ml (13.7% vs. 3.7% for those with 25OHD levels >30 ng/ml, *P* =0.007). Another study reported no association between cancer incidence and vitamin D status over a 10-year follow-up period after renal transplantation [35], although a single repletion study showed a decrease in cancer risk in RTRs treated with active vitamin D [36]. Whether these results can be explained by risk segregation with cancer type, particularly viral-related cancers, remains to be established.

The relationship between sun exposure and non-melanoma skin cancer also remains to be elucidated. Even though the role of sun exposure has been demonstrated, it should be note that VDR knockout (KO) mice develop UVB-induced skin cancers more rapidly and more frequently than wild-type mice, suggesting a potential protective role for 25OHD against non-melanoma skin cancers [37]. In RTR, regular application of sun protection factor (SPF) 50 sunscreen is associated with fewer skin lesions but also with lower 25OHD levels [38]. The association of higher levels of 25OHD with an increased risk of skin cancer can be explained by greater UV exposure [39]. These data highlight the difficulties of drawing conclusions using only epidemiological and not interventional studies.

### Anti-diabetic properties of vitamin D

According to the diagnostic criteria and post-transplantation delay, *de novo* T2DM occurs in 10% to 30% of RTR, mainly due to corticosteroid and tacrolimus treatment [40]. The potential effects of vitamin D on insulin secretion and insulin resistance are supported by experimental data [41]. First, VDR [42] and CYP27B1 [43] are expressed in pancreatic β cells, and vitamin D responsive elements (VDRE) have been identified in the promoter of the human gene encoding insulin [44]. Second, *in vitro* studies have shown that calcitriol stimulates transcription of the insulin gene, expression of insulin receptor, and glucose transport [41]. Third, VDR knockout (KO) mice have abnormal insulin secretion [45], and vitamin D_3_ supplementation increases glucose tolerance and insulin secretion in vitamin D-deficient rats [46]. In humans, serum 25OHD concentrations are inversely correlated with T2DM prevalence [41, 47–49]. Vitamin D insufficiency is also associated with increased glycated hemoglobin (HbA1c) levels [50] and resistance to insulin [47]. The influence of vitamin D on the resistance to insulin may be partly mediated by calcitriol, through control of the gene encoding adiponectin [51]. In a very recent paper, it was reported that vitamin D and calcium supplementation decreased serum interleukin (IL)-6 and tumour necrosis factor-α concentrations in patients with T2DM, and might thus improve systemic inflammation in this disease [52]. A recent meta-analysis of RCTs showed that active or native vitamin D supplementation improved fasting glycaemia and insulin resistance in patients with glucose intolerance, but had no effect on HbA1c levels [53]. However, another recent meta-analysis found no effects of vitamin D supplementation on glucose homeostasis or diabetes prevention, although a trend (*P* =0.06) towards reduction in fasting blood glucose in patients with pre-diabetes, and a significant reduction in homeostatic model assessment of insulin resistance (HOMA-IR) after exclusion of the studies that administered a single large dose of vitamin D were reported [54]. These authors indicated also that definitive conclusions may be limited because of heterogeneity in the studies, variable risk of bias, and the short-term follow-up duration of the available evidence to date, again emphasizing, as mentioned above for the potential effects of vitamin D on cancers, the need for large, well-conducted RCTs. To date, no study has reported the potential effect of active or native vitamin D on *de novo* T2DM after transplantation.

### Effects of vitamin D on the cardiovascular system

In comparison with the general population, RTRs have an increased cardiovascular risk secondary to both traditional and non-traditional risk factors (50-fold higher in RTRs) [55]. Observational and experimental data argue in favour of a potential protective role of vitamin D against cardiovascular disease. Cross-sectional studies have indicated that vitamin D deficiency is associated with arteriosclerosis and endothelial dysfunction in patients with end-stage renal disease [56]. Several prospective case–control studies have reported a strong association between low circulating levels of 25OHD and an increased risk of major cardiovascular events such as myocardial infarction, stroke, congestive heart failure [57, 58], and cardiovascular disease death [59–62]. These associations remained significant after adjustment for other risk factors for cardiovascular disease.

Possible explanations for these findings involve both direct and indirect effects of vitamin D on cardiovascular function. Direct effects are supported by the fact that cardiomyocytes, vascular smooth muscle cells, and endothelial cells express both VDR and the CYP27B1 enzyme [63]. Furthermore, genes upregulated during myocardial hypertrophy (such as atrial natriuretic peptide) possess VDREs, and are suppressed by calcitriol in animal and cell models [64]. Similarly, in cultured cells, calcitriol inhibits cardiomyocyte proliferation [65], and stimulates vascular smooth muscle cell proliferation and vascular endothelial growth factor expression by these cells [66]. Calcitriol also modulates contractile performances of isolated rat and mouse cardiomyocytes [67, 68].

Potential indirect consequences of vitamin D deficiency may underlie its role as a risk factor for cardiovascular dysfunction. VDR but also CYP27B1 KO mice have high BP levels and cardiac hypertrophy due to increased activation of the renin-angiotensin system (RAS) [69], and calcitriol treatment inhibits renin activation and decreases BP and cardiac hypertrophy in CYP27B1 KO mice [70]. Calcitriol also reduces the expression of the metalloproteinases (MMP) MMP2 and MMP9 [71]; expression of these two MMPs appears to promote vascular calcification [72]. In a recently published mendelian randomization study performed in 142,255 individuals, increase in an allele score based on variants of genes that affect 25OHD synthesis or substrate availability, and used as a proxy for 25OHD concentration, was found to be significantly associated with reduced odds of hypertension [73]. Even though no controlled interventional trials with clinical cardiovascular endpoints have been performed, numerous studies have shown either no or positive effects of vitamin D supplementation on intermediary parameters potentially related to cardiovascular health such as BP, endothelial or left ventricular function, and lipid profile [74]. Interestingly, a meta-analysis of 11 randomized trials either with active or native vitamin D confirmed this reduction in systolic BP in patients with hypertension, and suggested that native vitamin D produced a greater fall in systolic BP than activated compounds [75]. In that meta-analysis, positive effects of vitamin D supplementation on BP were modest and limited to patients with hypertension. Another potential cause explaining negative results of vitamin D trials on BP was suggested by the results of a recent 20-week study performed in 130 patients with moderate hypertension who received either 3,000 IU vitamin D_3_ daily or a placebo [76]. The primary objective, ambulatory BP (24 h BP), was not significantly modified in the vitamin D group compared with placebo in the intent-to-treat (ITT) analysis, although central BP, a secondary endpoint, was significantly reduced. However, in a *post hoc* analysis limited to the 92 patients with a baseline 25OHD level of less than 32 ng/ml, 24 h BP was modestly but significantly reduced. This may partly explain why ITT meta-analyses of studies on the effect of vitamin D on BP that include both patients with normal and patient with high BP, as well as patients with or without vitamin D deficiency, may appear negative, while the effect seems to be positive in patients with hypertension and vitamin D insufficiency.

Interventional studies targeted to the effect of vitamin D supplementation on major cardiovascular events and using death as a primary endpoint do not yet exist. In a secondary analysis of the RECORD trial on four pre-specified outcomes, vitamin D supplementation was found to protect against cardiac failure (HR =0.75; CI 0.58 to 0.97), but not against myocardial infarction or stroke [77]. However, several recently published meta-analyses of interventional studies (whose primary endpoint was not cardiovascular events) found no (positive or negative) effect of vitamin D supplementation on major cardiovascular events [77–79], although a slight, but significant decrease in all-cause mortality was reported [79–81]. To date, the few, weakly powered, observational studies performed in RTRs have found no robust association between serum 25OHD levels and cardiovascular risk factors [35, 82, 83]. The apparent discrepancy between the strong association of vitamin D deficiency with major cardiovascular events and the lack of strong evidence of a reduction in cardiovascular risk with vitamin D supplementation may be due to reverse causation, which frequently affects observational studies (low vitamin D being the consequence rather than the cause of the disease under study).

However, because vitamin D intoxication in humans may lead to vascular calcifications, the benefit/risk ratio of supraphysiologic dosages of vitamin D should be evaluated, especially in RTRs having an increased cardiovascular risk. Indeed, a biphasic effect of vitamin D on the risk of vascular calcifications is likely [84]. It has been recently reported from observational studies that the risk of all-cause mortality [85] and the risk of major cardiovascular events [86, 87] increased if serum 25OHD levels were below 20 ng/ml but also if levels were above 40 ng/ml. Although no causality can be concluded from observational studies, these results should incline the medical community to be cautious with regard to high-dose vitamin D supplementation and cardiovascular health.

## Methods

### Objectives

The VITALE study is designed to evaluate whether high doses of cholecalciferol in RTRs with vitamin D insufficiency has beneficial effects upon the late post-transplant outcome compared with low-dose supplementation. As a primary outcome, we will evaluate the impact of cholecalciferol on a composite endpoint including *de novo* DM (fasting glycaemia >7 mmol/l or glycaemia >11 mmol/l), major cardiovascular events (acute coronary heart disease, acute heart failure, lower-extremity arterial disease, cerebrovascular disease), *de novo* cancer, and patient death. Secondary objectives will compare the effects of high-dose versus low-dose cholecalciferol on BP and on BP control (number and dosage of antihypertensive drugs), echocardiography findings, infections (including cytomegalovirus, *Pneumocystis*, nocardial infection, cryptococcal infection, aspergillosis), acute rejection episodes, renal allograft function including Modification of the Diet in Renal Disease (MDRD)-v4 estimated glomerular filtration rate (eGFR) [88], proteinuria and graft survival, and mineral metabolism biologically (serum calcium, phosphate, 25OHD and PTH) and clinically (graft nephrolithiasis, bone mineral density, measured body weight, and incidence of fractures) relevant parameters.

We have noted that, according to the published literature, some vitamin D experts especially involved in the cardiovascular field consider that optimal 25OHD concentration for cardiovascular health probably lies within a narrow range of 30 to 40 ng/ml [89, 90]. We took this advice into account, and one of the main objectives of our VITALE trial is thus to evaluate whether our treatment scheme, which probably will increase the 25OHD concentration above 40 ng/ml in a significant percentage of patients, is safe, especially in terms of cardiovascular health.

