### Study population and sample size

The study sample will consist of 640 RTRs found to be lacking sufficient vitamin D (25OHD <30 ng/ml) 12 to 48 months post-transplantation with 320 subjects in each study group. Inclusion and exclusion criteria are detailed in the Appendix. The sample size calculation was performed according to the following assumptions: The principal criteria will be the occurrence of one of the events of the composite endpoint including *de novo* DM, major cardiovascular events, *de novo* cancer, and patient death. Over a 2-year follow-up period, we estimate, according to previous reports in the literature, that the incidence of a first event of the composite endpoint will be around 22% in our population (6% for *de novo* T2DM [91, 92], 6% for major cardiovascular events [93–95], 7% for *de novo* cancers [15, 96], and 3% for patient death). This 22% global estimated incidence does not take into account the fact that some patients may experience several events of the composite endpoint during the follow-up period. According to the results of the numerous observational studies showing an inverse association between 25OHD concentrations and various clinical events and to the results of the few interventional trials showing effects of high-dose vitamin D supplementation on these events (detailed above),we estimate that the overall decrease in the incidence risk of a first event of the composite endpoint will be around 40% in the high-dose group compared with the low-dose group (33% decrease for *de novo* DM, 40% decrease for major cardiovascular events and 50% decrease for *de novo* cancer). Thus, to demonstrate the reduction in the incidence of a first event of the composite endpoint from 22% in the low-dose group to 13% in the high-dose group, with a 90% power and 5% α risk error, 582 RTRs (291 in each group) will be required. Taking into account that 10% of patients will not be evaluable, a total of 640 RTRs will be required. The inclusion of a total of 480 RTRs would allow us to test the same hypothesis with a power of 80%.

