### Concomitant medication

Most RTRs are treated with an immunosuppressive therapy consisting of mycophenolate mofetil or sodicum mycophenolate, tacrolimus, or ciclosporin, with (in most cases) or without prednisone. Steroid boli, monoclonal antibodies, and polyclonal antibodies are administered to treat acute rejection episodes. Medications will be allowed during the study, with the exception of active or native vitamin D_2_, active or native D_3_, and multivitamin complexes likely to contain vitamin D. Drugs with anti-secretory and gastric-dressing properties will be allowed, but will have to be ingested at least 4 hours after cholecalciferol treatment.

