**Table 1 Tab1:** **Study procedures**

Date	Patients selection	Inclusion visit		M1	M2	M3	M6	M12	M18	M24
Cholecalciferol (high versus low dose)			**R = T0** ^**1**^	**Intensive phase (2 months)**		**Maintenance phase (22 months)**				
Written informed consent/checking of the inclusion and exclusion criteria		X								
Medical history entry		X								
Clinical examination, blood pressure, body weight and height		X				X	X	X	X	X
Current treatment		X				X	X	X	X	X
Notification of events constituting the primary composite criteria and the secondary criteria						X	X	X	X	X
Checking of treatment compliance						X	X	X	X	X
Notification of tolerance and side effects^2^						X	X	X	X	X
β-human chorionic gonadotropin if relevant		X								
25OHD	< 30 ng/ml	X				X^1^		X^1^		X^1^
Serum calcium^2^	<2.7 mmol/l	X				X	X	X	X	X
Serum phosphate^2^	<1.5 mmol/l	X				X	X	X	X	X
Fasting urinary calcium^2^		X				X	X	X	X	X
Fasting urinary creatinine^2^		X				X	X	X	X	X
Serum creatinine	<250 μmol/l	X				X	X	X	X	X
MDRD estimated glomerular filtration rate		X				X	X	X	X	X
Urinary protein/creatinine ratio		X						X		X
Urinary microalbumin/creatinine ratio		X						X		X
Fasting glycaemia	< 7 mmol/l	X				X	X	X	X	X
HbA1C		X						X		X
Liver function tests		X								X
Lipid profile		X						X		X
Complete blood count		X						X		X
Serum parathyroid hormone		X						X		X
Bone mineral density		X								X
Echocardiography^2^		X						X		X
DNA collection^3^		X								
Serum collection^3^		X				X		X		X

Table legend: M1 (M2, 3…): month one (two, three…) after randomization; MDRD: Modification of the Diet in Renal Disease; R: randomization; T0: time zero corresponding to the randomization of the patient.

^1^R: randomization represents the time 0 (T0). Intensive phase: cholecalciferol 100,000 IU or 12,000 IU every two weeks for 2 months. Maintenance phase: cholecalciferol 100,000 IU or 12,000 IU monthly for 22 months.

^2^Safety data. Echocardiography results will have to notify valvular calcifications.

^3^Samples for which the dosage (25OHD) and/or conservation will be centralized.

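### De novo diabetes, a component of the primary endpoint, is defined by glucose limits with no confirming value, no sample type for the second limit and no count of started antidiabetic treatment

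*Protocol article*

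**What the plan says.** The only definition of de novo diabetes is in Objectives: "fasting glycaemia >7 mmol/l or glycaemia >11 mmol/l". It is one of four components of the primary composite, which is analysed as time to first event in a Cox model (Statistical analysis).

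Table 1 lists "Fasting glycaemia" at inclusion and at months 3, 6, 12, 18 and 24, with a value below 7 mmol/l required at selection. Known type 1 or type 2 diabetes is excluded (Appendix). No random or post-load glucose test is scheduled. HbA1c is scheduled at inclusion, month 12 and month 24, and current treatment is recorded at every follow-up visit. Antidiabetic treatment appears in the analysis only as a secondary parameter among patients already classed as having de novo diabetes.

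Under Study population and sample size, diabetes contributes 6 of the 22 percentage points expected in the low-dose group, with an assumed "33% decrease for *de novo* DM". The composite is expected to fall "from 22% in the low-dose group to 13% in the high-dose group".

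**The concern.** A threshold rule without confirmation, applied repeatedly, picks up measurement variation as well as disease. A patient whose fasting glycaemia is stable just below 7 mmol/l satisfies the entry limit and then has five scheduled chances to exceed it. Because only the first event counts, a chance crossing also removes any later cardiovascular event, cancer or death of that patient from the primary comparison.

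The rule can also miss cases. A patient given antidiabetic drugs before either limit is exceeded, and kept below both, never becomes a diabetes event. The limit of 11 mmol/l has no sample type attached, so which readings it covers is open.

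Diabetes is 6/22 = 27% of the planned low-dose events. It is also tested on its own under the Hochberg procedure, and the HbA1c analyses are divided by whether diabetes is present. A loose definition therefore reaches beyond the composite.

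**Working it through.** **Inputs from the protocol article.** Event proportions 22% and 13%; 582 evaluable patients, 640 in total; 5% α with sidedness not stated; five follow-up readings of fasting glycaemia; limit 7 mmol/l.

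**Inputs assumed.** The documents give no within-patient variation, no baseline glucose distribution and no false-event rate. I take a within-patient coefficient of variation (CV) of 5 to 7%, normal and independent readings around a stable mean, and a range of false-event rates equal in both arms.

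**Step 1: the plan's own figure.** The plan states "with a 90% power and 5% α risk error, 582 RTRs (291 in each group) will be required". The hazard ratio implied by 22% and 13% is ln(0.87)/ln(0.78) = 0.560. Schoenfeld's formula, D = 4(z_α + z_β)²/(ln HR)², gives:
- one-sided 5%: 4 × (1.645 + 1.282)²/0.579² = about 102.2, so 103 events; 103/0.175 = 589 patients;
- two-sided 5%: 126 events; 126/0.175 = 720 patients.

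The stated 582 is approached only with a one-sided test, so I show power on both bases.

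**Step 2: chance of crossing 7 mmol/l without any change in the patient.** Per visit, p = 1 − Φ((7 − μ)/(CV × μ)). Over five visits, P = 1 − (1 − p)⁵.

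| True mean μ (mmol/l) | CV | p per visit | P over five visits |
|---|---|---|---|
| 6.5 | 5% | 0.062 | 0.27 |
| 6.5 | 6% | 0.100 | 0.41 |
| 6.5 | 7% | 0.136 | 0.52 |
| 6.0 | 5% | 0.0004 | 0.002 |
| 6.0 | 7% | 0.0086 | 0.042 |

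The risk is large close to the limit and falls off quickly below it. The trial-wide rate depends on how many patients sit close to 7, which is not given.

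**Step 3: effect on the primary comparison.** Suppose 3 percentage points of false events are added to each arm. This is an assumption and is not derived from step 2. The proportions become 25% and 16%, and HR = ln(0.84)/ln(0.75) = 0.606. Power = Φ(½√D × |ln HR| − z_α), with D = N × mean proportion:

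| N | Test | Power as planned | With 3 points added |
|---|---|---|---|
| 582 | one-sided | 89.9% | 86.2% |
| 640 | one-sided | 92.2% | 88.9% |
| 582 | two-sided | 83.2% | 78.1% |
| 640 | two-sided | 86.5% | 81.8% |

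The loss is 3 to 5 points.

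A second parametrisation takes a false-positive rate f per visit among event-free patients, so that each arm's proportion becomes p + (1 − p)(1 − (1 − f)⁵). With a one-sided two-proportion test at 291 per arm, power starts at 88.9%:
- f = 0.2%: 22.8% v 13.9%, power 87.3%
- f = 0.5%: 23.9% v 15.2%, power 84.9%
- f = 1%: 25.8% v 17.3%, power 80.8%
- f = 2%: 29.5% v 21.4%, power 73.0%

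**Step 4: missed treated cases.** If half of true diabetes were missed, the proportions become 22 − 3 = 19% and 13 − ½ × (6 × 0.67) = 11.0%. One-sided power at 291 per arm goes from 88.9% to 85.7%.

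**Step 5: what confirmation would do.** Take the patient of step 2 with μ = 6.5 and require two consecutive values above 7. With q = 1 − p, the chance of at least one such pair in five readings is 1 − (q⁵ + 5pq⁴ + 6p²q³ + p³q²). This is 1.5%, 3.7% and 6.6% for p = 0.062, 0.100 and 0.136, against 27%, 41% and 52% under the single-value rule.

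**The case against.** The strongest reply is that the definition is a parenthesis in a journal article that condenses a longer protocol. It gives diagnostic limits and does not say in words that one reading suffices. Table 1 has a separate row for notifying primary events, and outcome assessors are blinded, so events may not be triggered automatically by a laboratory value. The full protocol may contain a confirmation rule. This is fair and limits how firmly the point can be put. It does not remove it: the article fixes numeric limits for a primary component, and nothing in it adds confirmation or a treatment criterion.

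A reader might infer several stronger things that the documents do not support:

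- **That steroid-bolus or random readings will become false events in numbers.** The article does say "Steroid boli, monoclonal antibodies, and polyclonal antibodies are administered to treat acute rejection episodes", but only fasting glycaemia is scheduled, so such readings would come mostly from unscheduled tests at an unknown rate. The Background attributes de novo diabetes in this population mainly to corticosteroid and tacrolimus treatment, so a steroid-related rise is not plainly false.
- **That 27 to 52% of patients would be misclassified.** That range applies to a patient with a true mean of 6.5 mmol/l. At 6.0 it is about 0.2 to 4%.
- **That the result is biased towards benefit.** Participants, investigators and assessors are blinded, so the error should fall on both arms alike.
- **That every chance crossing is unrelated to treatment.** The Background cites a meta-analysis reporting improved fasting glycaemia with vitamin D in glucose-intolerant patients, and another finding only a trend in pre-diabetes. Some crossings may carry part of the effect.
- **That missed treated diabetes is a large loss.** Step 4 shows about 3 points of power even if half the cases were missed.

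The 6% planning rate may itself come from single-value definitions in the cited sources. If so, part of the dilution is already in the 22%.

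**Conclusion.** The point stands as a weakness of endpoint definition. As printed, a single value above a limit meets the definition, the sample type for 11 mmol/l is not named, and started treatment does not count. With five scheduled tests against the limit used at entry, some misclassification follows from applying the rule.

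The consequence is mainly dilution of the hazard ratio and loss of power. Its size cannot be settled from the documents. Three points of false events per arm would cost 3 to 5 points of power; 0.2 to 2% false positives per visit would take one-sided power at 291 per arm from 88.9% to between 87.3% and 73.0%. These figures rest on assumed rates, equal error in both arms, and a plan that does not already include such events in its 22%. The correction is worth making because it is cheap and diabetes carries over a quarter of the planned events.

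**What to change.** Reword the endpoint so that de novo diabetes counts when either of these holds:

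- a glycaemia above the stated limit is confirmed by the next available glycaemia or by the scheduled HbA1c, with the HbA1c limit specified in advance;
- antidiabetic treatment is started and is still recorded at the following visit.

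Name the sample type for the 11 mmol/l limit. State in advance which date the event takes, and how a first value at month 24, or the last value before drop-out, is classified. Keep the single-value definition as a sensitivity analysis.

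This is an endpoint rule for analysis and does not touch patient care. Glycaemia, HbA1c and current treatment are already in Table 1, so no new sampling is needed. The costs are slightly fewer diabetes events, a wait of up to six months between scheduled visits for confirmation, and reliance on HbA1c or a stated default for values at the last visit.
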